### Recruitment

Recruitment will occur at the Dental School, a reference place for dental treatment in children, and receives many patients who seek care or are referred from other units. Approximately 600 patients receive treatment per year. Participants will be randomly selected from this broad sample.

### Data collection, management and analysis

#### Data collection

A trained and calibrated (weighted Kappa value greater than 0.80)
examiner will perform the initial exams. Periodic checks (every 50 patients included in the study) of the calibration will be made in 10% of the sample.

Another evaluator, who has not participated in any previous phase of the study, will reassess the participants for the collection of outcomes after 12 and 24 months. This examiner will also be trained and calibrated before the start of follow-ups and periodically for every 50 evaluated participants. An intraclass correlation coefficient greater than 0.80 must be obtained before starting the assessments.

Regarding the collection of outcomes, the examiners will evaluate the children regarding: (1) the number of dental surfaces with decay in need of operative treatment, with dentinal involvement, cavitated or not; (2) the number of restored surfaces that need replacement (extensive failures, carious lesions around the restorations or complete loss of restorative material); (3) restorations in need of repair; (4) teeth with episodes of pain, need for endodontic treatment or extraction.

#### Data management

The groups will be coded in the analysis and data will be transferred to spreadsheets after the different phases of the study (baseline, 12 months, and 24 months). An external researcher will check the data for missing data, out-of-range values, and illogical or invalid responses weekly. In case of detection of protocol deviations, immediate solution may be established for guarantee the trial quality. In case of missed (or incorrect) data, data imputations may be indicated. After the publication of the main results, anonymous data will be shared in a public repository.

#### Data analysis

Outcomes will be analyzed as count variables. Shapiro–Wilk normality test will be performed. If it presents normal distribution, to compare the primary outcome between the two groups, Student's t-test will be performed. Regarding secondary outcomes, these will also be analyzed by Student's t-test if they have a normal distribution.

A multivariate analysis using negative binomial regression will also be used to compare groups, adjusting for socioeconomic and demographic variables (gender, age, number of children, family structure, and income). Two-tailed tests will be used for all analyses, and the significance level will be set at 5%.

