### Outcomes

The primary outcome will be a composite outcome representing the number of tooth surfaces requiring operative intervention in two years of follow-up. Thus, the primary outcome will be the sum of surfaces with new carious lesions involving dentin, restored surfaces that needed replacement, and those teeth needing endodontic treatment or extraction (accounting for 4 or 5 surfaces per tooth, for anterior or posterior teeth, respectively). If the tooth surface requires two types of treatment at different times, the treatment will be computed twice.

Secondary outcomes will be the components of the primary outcome considered separately: surfaces with new lesions involving dentin, restored surfaces in need of restoration replacement, teeth with episodes of pain, need of endodontic treatment and extraction. Besides that, costs accumulated for 24 months, health-related quality of life (HRQOL), and oral health-related quality of life (OHRQOL) will also be collected as secondary outcomes.

In order to assess the cost of going to the appointments during the 2 years of follow-up questions about travel will be collected: “What transport do you normally use to come to the appointments?”; “How many buses do you take to come?—If the person uses a bus.”; and “How long does it take, approximately, from leaving home until arriving at the dental school?”.

The HRQOL will be collected using the Brazilian version of the KIDSCREEN-52 [20] and for OHRQOL the Brazilian version of the Child Perceptions Questionnaire (CPQ) [21] will be used. The questionnaires will be applied by trained interviewers before the clinical examination.

For the economic evaluation, a specific analysis plan of economic economic will be prepared. The main economic hypothesis will be if using the multivariate (more complex) assessment may be an efficient manner of allocating resources. A societal perspective and a 24-month time horizon were adopted. Resources spent during the trial follow-up will be registered and then, appropriately valued as costs. The effects to be tested will be derived from the assessed outcomes: number of new operative interventions alongside 24 months, changes in DMFT after 24 months and Quality of life. Then, cost-effectiveness analyses will be performed.

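### The blanket count-variable rule does not fit the quality-of-life scores: the adjusted comparison and any non-normal case fall to negative binomial regression

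*Protocol article*

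**What the plan says.** The Data analysis section opens with "Outcomes will be analyzed as count variables" and names no exception. It then calls for a Shapiro–Wilk test and, if the primary outcome is normal, a t-test. It continues: "Regarding secondary outcomes, these will also be analyzed by Student's t-test if they have a normal distribution". The next paragraph adds: "A multivariate analysis using negative binomial regression will also be used to compare groups". That sentence is not tied to any particular outcome. The covariates are socioeconomic and demographic only: age, gender, income, family structure and number of children.

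The Outcomes section lists secondary outcomes of two kinds. The first are the components of the composite, which are numbers of surfaces and teeth. The second are described as follows: "costs accumulated for 24 months, health-related quality of life (HRQOL), and oral health-related quality of life (OHRQOL) will also be collected as secondary outcomes". On the instruments it says "The HRQOL will be collected using the Brazilian version of the KIDSCREEN-52", and it names the Brazilian CPQ for OHRQOL. On timing it says only: "The questionnaires will be applied by trained interviewers before the clinical examination". The same section announces a separate analysis plan for the economic evaluation.

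The Randomization section stratifies by age band and by caries experience (DMFS/dmfs up to 4, or above 4).

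**The concern.** A questionnaire score is not a number of events. Negative binomial regression models the log of the mean with variance μ + αμ², where α is zero or positive. For a scale score this has two consequences.

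- The effect is a ratio of scores. Readers of a quality-of-life result usually need a difference in points, and a ratio depends on where the scale places its zero.
- The standard error comes from a variance form that the score need not follow. If the score varies less than a Poisson count with the same mean, the model cannot go below the Poisson variance and the standard error is too large.

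At stake are the estimates and intervals for two secondary outcomes. The Outcomes section also lists quality of life among the effects for the cost-effectiveness analysis.

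**Working it through.** **1. Which method the text gives for KIDSCREEN-52 and CPQ**

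| Situation | Method stated |
|---|---|
| Score looks normal, unadjusted | Student's t-test |
| Score does not look normal, unadjusted | none named; only the negative binomial model remains |
| Adjusted comparison, either case | negative binomial regression |

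Only the first row suits a scale score.

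**2. The plan's own figure**

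The Sample size section concerns the primary outcome only: difference 5, SDs 15 and 10, two-sided 5%, power 80%.
n per group = (1.960 + 0.842)² × (15² + 10²) / 5² = 102.04, rounded up to 103. This reproduces the stated 103, and nothing in this point changes it. The plan gives no mean, SD or correlation for either questionnaire. Everything below is therefore illustration on assumed distributions, with 250 less 20% = 200 children, or 100 per arm.

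**3. Negative binomial against t-test**

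Scores were drawn from a normal distribution, rounded, and cut off at zero. There were 300 runs, arm was the only covariate, and the effect was either zero or 0.4 SD.

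| Assumed mean, SD | Type I error, NB / t-test | Power, NB / t-test |
|---|---|---|
| 50, 10 | 5.3% / 5.3% | 82% / 82% |
| 20, 12 | 2.0% / 5.0% | 64% / 80% |

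The simulation error is about √(0.05 × 0.95/300) = 1.3 percentage points at 5%, and √(0.64 × 0.36/300) = 2.8 points at 64%. The 16-point power gap is well outside that. A type I error below 5% means the fitted variance was too large, so the error is conservative.

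**4. A score with variance below its mean**

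Assume mean 50 and SD 6, so the variance is 36. The negative binomial model reduces to Poisson with variance 50. Its standard error is too large by √(50/36) = 1.18, or 18%.

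**5. Covariates**

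Of the two stratification factors, age is in the adjustment list and caries experience is not.

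**6. Baseline score, if it is collected**

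With correlation ρ between baseline and 24 months, the residual variance is (1 − ρ²) of the unadjusted variance. The unadjusted detectable difference at 80% power is 2.802 × √(2/100) = 0.396 SD, and adjustment multiplies it by √(1 − ρ²).

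| Assumed ρ | Variance cut | Detectable difference | Power at 0.4 SD |
|---|---|---|---|
| unadjusted | none | 0.396 SD | 81% |
| 0.3 | 9% | 0.378 SD | 84% |
| 0.5 | 25% | 0.343 SD | 90% |
| 0.7 | 49% | 0.283 SD | 98% |

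**The case against.** The best defence is that the count wording was meant for the primary outcome. The Abstract attaches its count label to the surface composite and then names the negative binomial model. The Data analysis section never says that this model is fitted to KIDSCREEN-52 or CPQ, and it describes the model as an addition to the t-test. A t-test on roughly normal scores gives a valid mean difference.

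This defence limits the point but does not remove it. The opening sentence of Data analysis is plural and unrestricted, its paragraph goes on to the secondary outcomes, and no other adjusted model or non-normal route is given. If the narrower meaning was intended, the text should say so.

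A reader might infer three stronger things, which the documents do not support.

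- *That costs will be analysed as counts.* Costs are a secondary outcome, but the Outcomes section sends the economic evaluation to its own plan, which is not shown. The Data analysis section cannot be said to fix the cost model.
- *That the quality-of-life error bars will be wrong in general.* The t-test branch is sound, and in one of the assumed distributions the two methods agree.
- *That the trial wrongly ignores baseline quality of life.* The visible text does not say the questionnaires are given at baseline, and the timeline figure is not shown. An unadjusted randomised comparison is in any case less precise, not invalid.

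Nor do the documents say that quality of life will decide between the methods. The Discussion names the views of patient and dentist, and the workplace setting, as possible deciding factors.

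**Conclusion.** The point holds as a mismatch between a stated rule and two named secondary outcomes. As written, the adjusted analysis of KIDSCREEN-52 and CPQ, and any analysis of non-normal scores, falls to a count model. Depending on the score distribution, the consequence ranges from no loss to a conservative test. The illustrations give power of 64% against 80% in one case and a standard error 18% too large in another. None of them showed an excess of false positives. All these sizes rest on assumed means and SDs.

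The omission of caries experience from the adjustment is plain from the text. The gain from a baseline score depends on that score being collected. The primary analysis and the sample size do not change.

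**What to change.** In the Data analysis section:

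1. Limit the count-variable statement and negative binomial regression to the composite and its surface and tooth components.
2. Analyse KIDSCREEN-52 and CPQ by linear regression of the 24-month score on arm and the two randomisation strata (age band and caries experience), plus the baseline score if it is collected. Report a mean difference with robust standard errors and a 95% confidence interval, without a normality pre-test.
3. For costs, refer to the separate economic analysis plan.

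This takes two or three sentences. It needs no new data and no extra children, and should be settled before unblinding.

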**Methods:**

This is a randomized, double-blind, controlled, parallel-treatment trial protocol. Two groups will be tested for two forms of caries risk assessment: an individualized and detailed multivariate method based on the guidelines of the Caries Care International 4D and another simplified process, based only on caries experience in primary and/or permanent dentition, considering the presence of decayed, missing and filled teeth using the DMFT/dmft index. Participants will be children aged 8 to 11 years, followed up at 12 and 24 months. The primary outcome will be a composite outcome representing the number of tooth surfaces requiring operative intervention (account variable). In addition, the Shapiro–Wilk normality test and Student's t-test will be performed. A multivariate analysis using negative binomial regression will compare groups in the intention-to-treat population, considering a two-tailed significance level of 5%.

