### Sample size

The sample estimation was based on the primary outcome, which is the number of tooth surfaces in need of surgery during follow-up. Therefore, the following possibilities were considered to compose this outcome:New caries lesions;Restorations in need of replacement;Dental extractions (5 surfaces per tooth);Resolution of pain episodes and/or need for endodontic treatment (5 surfaces per tooth).

To perform the sample calculation, incidence data were collected for all possibilities in the literature, reaching an average occurrence of 17.6 new decayed surfaces in 2 years [22], 10% failure of occlusal-proximal and composite resin and glass ionomer occlusal restorations, which gives an average of 0.1 surface with the need to change for occlusal restorations and 0.2 surfaces in 2 years [23], 0.08 tooth extractions for caries in two years, totaling 0.2 surfaces [24] and 0.2 pain episodes in 2 years on average, leading to an average of 1 surface treated in 2 years. Thus, the estimate of surfaces in need of surgical treatment in 2 years is an average of 19. It was considered that the reduction of 5 surfaces in need of treatment would be a significant number. The expected mean for the test group would be 14. The expected standard deviation values for the control and test groups are 15 and 10, respectively [22–24]. Considering a significance level of 0.05 and a power of 0.80, using a two-tailed test, the minimum number of children per group calculated was 103. Considering a sample loss of 20%, the final rounded number required of 250 children was reached.

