### Study status

Suspended: Study halted prematurely because of 2019 Novel Coronavirus (COVID-19) pandemic but potentially will resume.

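### The primary t-test depends on a normality test that the planned count will almost certainly fail; no replacement is named, and the negative binomial model run alongside is not declared primary

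*Protocol article*

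**What the plan says.** The Data analysis section opens with "Outcomes will be analyzed as count variables". It then prescribes a Shapiro-Wilk test and attaches a condition to the main comparison: "If it presents normal distribution, to compare the primary outcome between the two groups", Student's t-test is used. Secondary outcomes follow the same conditional route. Nothing is said about what happens if normality is rejected.

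The section continues: "A multivariate analysis using negative binomial regression will also be used to compare groups". The listed adjustment variables are gender, age, number of children, family structure and income. Both analyses share one error level: "Two-tailed tests will be used for all analyses, and the significance level will be set at 5"%. Neither is called primary or supportive.

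The Methods paragraph of the abstract differs. It lists Shapiro-Wilk and the t-test without the condition, and adds: "A multivariate analysis using negative binomial regression will compare groups in the intention-to-treat population". It gives no ranking either.

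Two other sections bear on this. Sample size plans a comparison of means: 19 against 14 surfaces, SDs 15 and 10. Randomization, implementation, and blinding stratifies by age group and by DMFS/dmfs (up to 4, above 4).

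**The concern.** Whether a t-test is run depends on a pre-test of the trial's own data, and one of the two branches is empty. If the pre-test nearly always rejects, the empty branch is the one the trial will take. The analyst must then choose an unadjusted test with the data in hand, or fall back on a regression that the plan has not declared decisive.

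Three things are left open: the test, the effect measure (the sample size uses a difference in mean surfaces, while negative binomial regression gives a rate ratio) and the power. The Discussion expects the two methods to give very similar results, so a non-significant finding is plausible. It would be hard to interpret if test and power had been settled after the data were seen.

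The one comparison that does not depend on the gate also leaves out caries experience, which the trial thought important enough to stratify on.

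**Working it through.** **Inputs.** From Sample size: "the estimate of surfaces in need of surgical treatment in 2 years is an average of 19" for control, 14 for the test group, SDs 15 and 10, difference 5, 103 per group. Also "Considering a significance level of 0.05 and a power of 0.80, using a two-tailed test". Equal allocation is assumed; it is not stated outright.

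**1. The plan's own figure.** Comparing two means with unequal SDs, normal approximation:

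n = (15² + 10²) × (1.960 + 0.842)² / 5² = 325 × 7.849 / 25 = 102.04, so 103 per group.

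The stated 103 is reproduced; power at 103 is 0.804. The section says only that the test is two-tailed and does not name a t-test, but the figure follows from a comparison of means.

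**2. Can the outcome look normal?** A normal distribution with these values would put children below zero:
- control: Φ(−19/15) = Φ(−1.27) = 10.3%
- test: Φ(−14/10) = Φ(−1.40) = 8.1%

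A count cannot do that. For a negative binomial with the same mean m and SD s, k = m²/(s² − m), p = k/(k + m), and skewness = (2 − p)/√(k(1 − p)):
- control: k = 361/206 = 1.75, skewness 1.51
- test: k = 196/86 = 2.28, skewness 1.33

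**3. How often does Shapiro-Wilk reject?** Simulation at the 5% level, 103 per arm, 4,000 runs per shape. The plan does not say whether the test is applied by arm or pooled, so both are shown.

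| Assumed shape | Control | Test | Pooled |
|---|---|---|---|
| Negative binomial, planned means and SDs | 100% | 99.98% | 100% |
| Zero-truncated normal, planned means and SDs | 100% | 99.9% | 100% |
| Rounded normal floored at zero | 97% | 89% | 100% |
| Rounded normal with negative values (impossible; reference only) | 5.1% | 6.3% | 30% |

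For the floored normal, at least one arm is rejected in 99.7% of runs. With 125 per arm, rejection in the three non-negative shapes is the same or higher.

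**4. Does the replacement matter?** Negative binomial counts, 103 per arm, planned means and SDs:

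| Test | Power | Runs |
|---|---|---|
| Student's t or Welch | 82% | 4,000 |
| Mann-Whitney | 62% | 4,000 |
| Negative binomial regression, unadjusted | 83% | 1,200 |

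On the 1,200 data sets used for the regression, the t-test had 81%. The Monte Carlo standard error there is √(0.82 × 0.18/1200) = 1.1 points, so the t-test and the regression are close. The gap of about 20 points to Mann-Whitney is far beyond simulation error.

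**5. Error rates under no effect** (both arms mean 19, SD 15). With 4,000 runs: t-test 5.1%, Welch 5.1%, Mann-Whitney 4.9%. With 1,200 runs: t-test 5.3%, unadjusted negative binomial 5.4%, and 5.7% if either significant result is accepted. The two disagreed in 0.6% of null trials and 2.4% of trials with the planned effect.

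**6. Strata against covariates.** Randomisation uses age group and DMFS/dmfs category. The regression list contains age but no measure of caries experience.

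**The case against.** The best defence is that negative binomial regression is already the effective main analysis. It is the only comparison not behind the gate, its covariates are listed, it suits a count, and the abstract ties it to the intention-to-treat population and the 5% level. A separate analysis plan could confirm this. Part of that stands: a sensible model is in the plan, and the defect is smaller than having no usable analysis. It does not remove the defect. The article says the model is used as well, not instead, and it fixes a data-dependent rule with an empty branch. That is a badly stated rule rather than a detail left for later.

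A reader might infer more than the document supports:
- **That the t-test is invalid for these data.** It is not: its type I error is about 5% at 103 per arm. The fault is the gate.
- **That two unranked tests seriously inflate the error rate.** The figure without invented inputs is 5.7%, within simulation error of either test alone. It arises only if the t-test is run ungated, as the abstract may be read; under the Data analysis section the t-test would seldom run. The added effect of covariate adjustment cannot be computed, because no covariate effects are given.
- **That unequal follow-up is being ignored.** Study status says "Study halted prematurely because of 2019 Novel Coronavirus (COVID-19) pandemic but potentially will resume" but gives no follow-up lengths. Outcomes and Timeline fix a 24-month horizon, and the 20% allowance is for sample loss, which is a missing-data matter.
- **That costs and quality-of-life scores will be modelled as counts.** Outcomes defers the economic evaluation to its own analysis plan, and the Data analysis section gives secondary outcomes a t-test route. The count sentence is loose wording.

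**Conclusion.** The point holds and should be fixed. The named primary test would almost never be reached, its replacement is not stated, and the one ungated model is not declared primary and omits a stratification factor.

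The main consequence is uncertain power and an uncertain effect measure: about 62% to 83% power depending on how the empty branch is filled, against the planned 80%. False-positive risk is a minor part.

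This rests on assumptions. The document gives no outcome distribution, so near-certain rejection depends on the shape. It was at least 99.9% for both shapes matched to the planned means and SDs, and 89% to 97% by arm (100% pooled) for a normal floored at zero. The power figures assume negative binomial counts with the planned values. Mann-Whitney is a common substitute after failed normality, not one the plan names.

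**What to change.** Remove the Shapiro-Wilk condition and replace the first part of the Data analysis section with wording such as:

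*The single primary analysis is negative binomial regression of the 24-month count of surfaces requiring operative intervention, in the intention-to-treat population, with terms for treatment group, age group and DMFS/dmfs category as used in randomisation, and the prespecified socioeconomic and demographic covariates. The rate ratio and the model-based difference in mean surfaces will be reported with 95% confidence intervals. An unadjusted t-test, run whatever the shape of the distribution, is supportive.*

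State which of the currently listed covariates stay in the primary model, so that none is dropped silently. Bring the abstract into line with the same ranking.

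The cost is small. The model is already in the plan, and the strata are recorded at randomisation. Unadjusted negative binomial regression has about 83% power at the planned values, so this change does not call for a larger sample. The mean difference keeps the result on the 5-surface scale of the sample size; the planned effect as a rate ratio is 14/19 = 0.74. The change must be dated before outcomes are analysed.
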